### Participant timeline

For the schedule of enrolment, interventions, and assessments, see Table 1.

**Table 1 Tab1:**
[figure not shown]
Schedule of enrollment, interventions, and assessments

*Follow-up (1)—the first postoperative day

**Follow-up (2)—the first week after the procedure

***Follow-up (3)—postoperative day 30

### Sample size

Considering that this is a superiority study, the sample size was calculated using a 1-sided Blackwelder test. According to published data, the incidence of opioid intake after hemorrhoidectomy varies from 20 to 30% [7]. The expected incidence of opioid intake after hemorrhoidectomy with preemptive analgesia is not more than 10%. The purpose of this study is to show that the opioids intake in patients with preemptive analgesia is lower than without it. Considering that *a* = 0.05. the statistical power of the study is 80%, the patients are randomized into 2 groups with 1:1 allocation ratio, the noninferiority margin *D* = 5%, and the required sample size is 144 patients (72 patients in each of the 2 groups).

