### Study design and setting

This is a prospective, randomized, double-blind, unicenter, superiority, parallel-group 2-arm study with 1:1 allocation ratio conducted in the surgical department of Moscow Research Educational Center of the Lomonosov Moscow State University. It is in the recruitment stage. We are anticipating 144 patients of all genders from 18 to 75 years old in total who come to the clinic. Thus, in this case, a uni-center design can assure sufficient patient recruitment.

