### Statistics

The ITT analysis included all randomized patients treated for at least 1 week, who were evaluated for efficacy at baseline and at least once at subsequent evaluation points during the study. The PP-analysis will exclude from the full analysis all the non-compliant patients, patients who received incomplete treatment, and patients who refused further treatment after randomization.

Quantitative variables are described as means with standard deviations, medians, range, or interquartile range as appropriate. Categorical variables are described in absolute numbers and percentages. The statistical analysis of the quantitative variables, with independent groups, is performed with the parametric Student’s *t* test, providing that its conditions for application are met. Otherwise, the non-parametric Mann-Whitney *U* test is used. Statistical analysis for categorical variables is performed using the Pearson *χ*^2^ test or the Fisher exact test. Specifically, the above methods are used to compare the two groups in terms of baseline characteristics in order to assess whether the randomization has been effective. Ninety-five percent confidence intervals for the ratio will be reported. In all cases, the level of significance will be the usual 5% (*α* = 0.05).

This study has a low risk of selection bias due to the use of a computer random number generator. Central allocation and the use of sequentially numbered drug containers of identical appearance allow to achieve a low risk of deviations. Performance bias may be considered as having an average risk due to blinding only participants of the study, the personnel is not blinding. Blinding of outcome assessment is ensured, so detection bias is unlikely. Attrition bias could probably appear because of the difficulty of collecting data from patients outside the hospital or the refusal of future treatment and visiting the doctor during follow-up.

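### The sample size section sizes a superiority trial with a non-inferiority margin and no fixed control rate, so its unqualified 80% power holds only toward the 30% end of its own range

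*Protocol article*

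**What the plan says.** The section Study design and setting calls the trial a superiority study: "This is a prospective, randomized, double-blind, unicenter, superiority, parallel-group 2-arm study with 1:1 allocation ratio". The section Sample size repeats this and gives the purpose as showing lower opioid intake with preemptive analgesia.

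The inputs in Sample size are:
- Method: "Considering that this is a superiority study, the sample size was calculated using a 1-sided Blackwelder test".
- Control rate: "the incidence of opioid intake after hemorrhoidectomy varies from 20 to 30" per cent. No single planning value is chosen.
- Ketoprofen rate: "The expected incidence of opioid intake after hemorrhoidectomy with preemptive analgesia is not more than 10" per cent.
- One-sided alpha 0.05, and "the statistical power of the study is 80" per cent.
- "the noninferiority margin" D, set at 5%.
- Result: "the required sample size is 144 patients (72 patients in each of the 2 groups").

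The Statistics section plans Student's t or Mann-Whitney tests for quantities and Pearson chi-square or Fisher exact tests for categories, with 95% confidence intervals. On the error rate it says "In all cases, the level of significance will be the usual 5" per cent. It mentions no margin and does not state sidedness.

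**The concern.** A non-inferiority margin of 5 points tests whether ketoprofen is no more than 5 points worse than placebo. The trial wants to show that ketoprofen is better, and its planned tests compare the arms against zero difference. At 20% versus 10%, adding the margin raises the planning distance from 10 points to 15, which cuts the required size to less than half.

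This is the only power statement for the trial, and it carries no condition although the control rate is left as a range. If the control rate is at the low end, a non-significant result would be read as coming from a trial with 80% power when the true figure is about half that.

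**Working it through.** **Inputs** (all from Sample size): control rate pC = 0.20 to 0.30; ketoprofen rate pT = 0.10, the stated upper bound; one-sided alpha 0.05; power 0.80; D = 0.05; 72 per arm.

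**1. The plan's figure by the plan's method.** Per arm, n = (z_alpha + z_beta)² × [pC(1−pC) + pT(1−pT)] / (pC − pT + D)².
- At 20% versus 10%, (1.645 + 0.842)² = 6.183, the variance term is 0.16 + 0.09 = 0.25, and the distance is 0.10 + 0.05 = 0.15. So n = 6.183 × 0.25 / 0.0225 = 68.7, or 69 per arm (138 in total).
- With a pooled null variance, n = (1.645 × √0.255 + 0.842 × √0.25)² / 0.0225 = 69.6, or 70 per arm (140 in total).
- Non-inferiority power at 72 per arm: 0.15 / √(0.25/72) − 1.645 = 0.90, which gives 82%.
- At control rates of 25% and 30% the unpooled formula gives 43 and 30 per arm.

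The stated method at 20% versus 10% therefore comes close to 72 without hitting it.

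**2. Another route to 144.** Take plain superiority, two-sided 5%, 30% versus 10%, with continuity correction.
- Uncorrected: (1.960 × √0.32 + 0.842 × √0.30)² / 0.04 = 61.6.
- Corrected: (61.6/4) × [1 + √(1 + 4/(61.6 × 0.20))]² = 71.2, or 72 per arm. This is exactly 144 in total, but it is neither one-sided nor Blackwelder and uses no margin.

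**3. D read as a superiority margin.** The distance becomes pC − pT − D = 0.05, 0.10 or 0.15. The formula in step 1 then gives 619, 172 and 83 per arm, so this reading does not produce 72.

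**4. Size needed for superiority with no margin** (unpooled, distance pC − pT), for control rates of 20, 25 and 30%:
- One-sided 5%: 155, 77 and 47 per arm.
- Two-sided 5%: 197, 97 and 59 per arm. For example, at 20% versus 10%, 7.849 × 0.25 / 0.01 = 196.2.

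**5. Superiority power of the 72 per arm.** Both binomial distributions were enumerated, with pT = 10%.

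| Test | pC = 20% | pC = 25% | pC = 30% |
|---|---|---|---|
| Pearson, two-sided 5% | 39% | 68% | 87% |
| Fisher, two-sided 5% | 32% | 60% | 83% |
| Pearson statistic, one-sided 5% | 53% | 78% | 93% |
| Fisher, one-sided 5% | 43% | 71% | 89% |

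**6. Where 80% is reached.** At a control rate of 28%, two-sided Pearson gives 81% and two-sided Fisher 75%. Fisher passes 80% only at about 30%.

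**7. A ketoprofen rate below the bound.** At 20% versus 5%, exact two-sided power is 81% (Pearson) or 74% (Fisher).

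**The case against.** Four points can be made for the plan, or against a harsher reading of it.

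*The origin of 144 is not proven.* A reader might infer that 72 per arm can come only from the non-inferiority margin. Step 2 shows otherwise: an ordinary superiority formula at 30% versus 10% gives 72 exactly, while the stated method gives 69 or 70. This stands. It does not rescue the text, because if that was the route, Sample size describes the wrong calculation.

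*The trial is not underpowered throughout.* A reader might infer that it simply lacks 80% power. At 30% versus 10%, inside the stated range, power is 83% or more under every test in the table. The 39% figure combines the lowest control rate, a two-sided test and exactly 10% on ketoprofen. The article does not state a two-sided test. The usual 5% with 95% intervals implies it, while Sample size says one-sided, which gives 53%. A ketoprofen rate below 10% would also raise power. All of this stands and makes the finding conditional.

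*The margin is not a success rule.* A reader might fear that superiority will be claimed against a bound of 5 points worse. That bound would be met in about 27% of trials with 10% in both arms, and in about 19% with 20% in both. Nothing in the article proposes such a rule, and the Statistics section has no margin, so this risk is no part of the finding.

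*The proportion with any opioid is not the stated primary outcome.* The main outcome measures section names the quantity of opioid per day over the first week. The powers above therefore apply to the endpoint used for sizing. This stands, and the correction has to say so.

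**Conclusion.** The point holds in conditional form. The sample size section combines a superiority aim with a non-inferiority margin and test, fixes no control rate, and states 80% power without qualification. The calculation as described does not support 80% superiority power over the stated range.

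With 72 per arm and 10% on ketoprofen, 80% is missed at control rates of 20% and 25% under every test examined. At 20% the exact power is 32 to 39% two-sided, or 53% with the one-sided Pearson statistic. For two-sided tests, 80% is reached from a control rate of about 28% (Pearson) or 30% (Fisher).

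These figures assume full follow-up of 72 per arm, a ketoprofen rate at its stated upper bound, and a comparison of the proportions with any opioid intake. They do not show which formula produced 144, and they are not the power of an analysis of daily opioid quantity.

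**What to change.** In Sample size:
- Delete the non-inferiority margin and the Blackwelder test.
- State the null hypothesis as zero difference in the proportion with any opioid intake.
- Name the test and sidedness that the analysis will use. Two-sided 5% would match the Statistics section.
- Restate the power of the existing 144 patients across control rates of 20 to 30% against 10%: 39, 68 and 87% for two-sided Pearson, or 32, 60 and 83% for two-sided Fisher. Alternatively, name the control rate at which 80% holds (about 28% or about 30%, respectively).
- Say that these figures refer to the any-opioid proportion, and reconcile that with the daily opioid quantity named as primary outcome in the main outcome measures section. The restated power should not be used to change the primary endpoint without saying so.

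The cost is a change of wording and a less favourable stated power. No extra patients are needed.

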### Recruitment

All patients diagnosed with HD II–III stage will be considered for this study.

### Assignment of interventions

Participants will be randomly assigned to either control or experimental group with a 1:1 allocation ratio using cluster randomization with a computerized random number generator. All subjects will be allocated any interventions. The experimental group receives a tablet with 100 mg ketoprofen, the control one receives a tablet containing starch per os 2 h before surgery (72 participants per arm) (see Fig. 1). The investigator who does not operate generates the allocation sequence, enrolls participants, obtains informed consent, and assigns participants to interventions. The surgeon and the anesthesiology team are blinded.

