### Eligibility criteria

Every patient included in the study must meet the following criteria:
Symptomatic hemorrhoids grade III–IVPlanned surgery: Milligan-Morgan hemorrhoidectomy

Patients who had contraindication or technical inability to perform subarachnoid anesthesia or other somatic diseases (history of peptic ulcer diseases and gastrointestinal bleeding and other acute or decompensated organ pathology) or refused to participate and pregnant women are not included. The written voluntary informed consent to participate (Additional file 3) is obtained from all eligible patients before randomization.

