### Consent or assent

A member of the research team will obtain the consent form. All participants will be able to address their questions about the study to one of the members of the research team.

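### One investigator generates the allocation sequence and also enrols, so the enroller can know the next arm; this is hard to reconcile with the claimed central allocation

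*Protocol article*

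**What the plan says.** Under Assignment of interventions, the protocol article gives four tasks to one role: "The investigator who does not operate generates the allocation sequence, enrolls participants, obtains informed consent, and assigns participants to interventions". The sequence is described as "1:1 allocation ratio using cluster randomization with a computerized random number generator". The only staff named there as blinded are those in this sentence: "The surgeon and the anesthesiology team are blinded".

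The Statistics section makes two separate claims about bias. On selection: "This study has a low risk of selection bias due to the use of a computer random number generator". On deviations: "Central allocation and the use of sequentially numbered drug containers of identical appearance allow to achieve a low risk of deviations". The same paragraph then describes blinding as "blinding only participants of the study, the personnel is not blinding".

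Two other sections touch on the sequence of events. Eligibility criteria says that written consent "is obtained from all eligible patients before randomization". Consent or assent says: "A member of the research team will obtain the consent form". No section names an independent person who holds the list, or who fills and numbers the containers.

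**The concern.** Allocation concealment has one purpose: the person who decides whether and when the next patient enters must not be able to foresee that patient's arm. Giving list generation and enrolment to the same role removes the separation on which this depends.

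Foreknowledge could matter in this trial because some prognosis is visible before enrolment. Stage, number of enlarged nodes and symptoms are listed as baseline characteristics, and the Surgical technique section allows one to three nodes to be removed. Opioid use, the primary outcome, plausibly depends on the extent of surgery. If patients expected to have more pain were approached, deferred or timed differently according to the coming arm, the groups would differ before the tablet was given. The article's assurance of low selection bias would then have no basis.

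**Working it through.** The point rests on the text, so the check sets the statements side by side. The article gives no figure to reproduce.

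1. **Who can know the next arm?** Assignment of interventions has the non-operating investigator generate the sequence. The author of a list can know its order unless a further step takes it out of that person's hands. No such step is described.

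2. **Does consent before randomization protect?** No. It fixes the order of two events for a given patient. A person who has the list can know the next arm before approaching that patient at all.

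3. **Do the numbered, identical containers protect?** They hide the arm from anyone who lacks the key linking numbers to arms, so they can protect the surgeon, the anesthesiology team and the patient. They do not protect against someone who holds that key.

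4. **Does the random number generator protect?** It makes the sequence unpredictable to those who have not seen it. It does not conceal the sequence from the person who ran it, so low selection bias does not follow from the reason the article gives.

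5. **Does blinding protect?** The assignment section lists the surgeon and the anesthesiology team, and not the enrolling investigator. The Statistics section says personnel are not blinded. These two statements also disagree with each other, and neither covers the enroller. The blinded analyst mentioned under Data collection, management, and analysis comes in after selection is complete.

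6. **Is central allocation compatible with this?** Central allocation normally means that someone away from the point of enrolment releases the assignment. Here the enroller generates the list and assigns, in a single-centre trial.

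**Size.** The documents give no opioid rates by stage or node number and no degree of steering, so the bias cannot be calculated. The general relation is: shift in risk difference = imbalance in the share of high-risk patients × (risk in high-risk patients − risk in low-risk patients). The figures below are assumptions that show scale only.

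- Assume risks of 30% and 10% and an imbalance of 15 percentage points: 0.15 × (0.30 − 0.10) = 0.03, or 3 points. The Sample size section plans for 20–30% against at most 10%, a difference of 10 to 20 points. Three points is 3/10 = 30% of that difference at the low end and 3/20 = 15% at the high end.
- Assume risks of 40% and 10%, half of patients high-risk overall (mean 25%), no drug effect, 72 per arm and a one-sided 5% test. Imbalances of 10, 20 and 30 points give shifts of 0.30 × 0.10 = 3, 0.30 × 0.20 = 6 and 0.30 × 0.30 = 9 points. The chance of a false positive rises from 5% to about 11%, 21% and 35% (0.109, 0.207, 0.345).

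**The case against.** The strongest reply is that the two sections describe different things: one says who does the tasks, the other by what mechanism. The mechanism includes numbered containers of identical appearance, which is a recognised way to conceal allocation. The text does not say that the investigator kept the list or filled the containers. The article is also condensed, and since the consent section refers only to a member of the research team, the singular investigator may be loose wording.

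Part of this stands. A reader might infer that the enroller did know each assignment, or that concealment was absent altogether. The documents support neither. They show that the enroller can know, and the containers may well have concealed the arm from others. A reader might also merge the two bias claims, but low selection bias is credited to the generator alone, while central allocation and the containers are credited with a low risk of deviations.

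A further tempting inference is that no analysis could repair the harm. That is too strong. Stage and number of enlarged hemorrhoids are recorded at baseline, and the Statistics section plans to compare baseline characteristics between groups.

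The reply does not remove the point. The article affirmatively assigns the four tasks to one role, so this is not a detail left to a fuller document, and no section names anyone else who could hold the key.

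**Conclusion.** The point holds in this form: the process as written does not secure concealment of the next arm from the person who enrols. It is hard to reconcile with the claimed central allocation and does not support the claim of low selection bias.

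The conclusion is about exposure to bias, not evidence of it. It assumes that the role described in the assignment section is what was practised and that the list stayed accessible to that role. If an independent party in fact held the list and prepared the containers, the defect is one of wording only.

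The size cannot be determined from the documents, and the scale calculations rest wholly on assumed rates and imbalances. Imbalance on stage and node number would be visible and open to adjustment; steering on unrecorded features would be neither. The randomized comparison depends on this step, so the matter should be settled before results are interpreted.

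**What to change.** First establish which section describes actual conduct, then reconcile both to it. Rewriting the assignment section without that step could misdescribe how patients already enrolled were allocated.

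**Patients still to be enrolled.** Have someone with no role in enrolment, treatment or assessment, for example the pharmacy, generate and hold the list and prepare the identical coded containers. The enrolling investigator takes the next number only after consent and registration.

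**Patients already enrolled.** The article reports recruitment from April 2020, expected to finish by the end of December 2021, so a new procedure cannot restore concealment for them. Report who held the list and who prepared the containers. If it was the enroller, withdraw the statement of low selection bias. Add an analysis of the primary outcome adjusted for baseline stage and number of nodes, and state that it cannot correct for unrecorded factors.

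**Cost.** One task moves to existing staff or the pharmacy, the text is amended, and one analysis is added using data already collected. The sample size is unaffected. If recruitment has closed, only the reconciliation, disclosure and added analysis remain.

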**Fig. 1 Fig1:**
[figure not shown]
Trial flow diagram

All relevant data from patient charts except patients’ names will be transferred into an electronic case report form (eCRF). The eCRF should contain results of all the screening procedures, including patient history and demographics, imaging studies, filled-out questionnaires, operation notes, and postoperative rounds during a patient stay in the surgical ward.

### Data collection, management, and analysis

All data will be collected prospectively using eCRFs designed for this trial. The reasons for withdrawal will be documented. The investigator will attempt to contact each participant at least 3 times during each follow-up window before declaring them lost for observation. The study exit form will be recorded in the eCRF. All prior data will be analyzed within the research.

All patients will receive clarifications of all the study procedures and will be able to discuss them with the primary investigator. All patient data will be handled according to the principles of doctor–patient confidentiality; the subjects will be anonymized and analyzed with individual identifier numbers transcribed into eCRF.

Data analysis will be performed by one of the researches who is blind to the randomization by using Statistical Product and Service Solutions (SPSS) Statistics for Windows, version 20.0 (IBM Corp., Armonk, NY, USA). Continuous variables will be presented as mean and standard deviation, and categorical variables will be presented as frequency or percentage.

### Statistics

The ITT analysis included all randomized patients treated for at least 1 week, who were evaluated for efficacy at baseline and at least once at subsequent evaluation points during the study. The PP-analysis will exclude from the full analysis all the non-compliant patients, patients who received incomplete treatment, and patients who refused further treatment after randomization.

Quantitative variables are described as means with standard deviations, medians, range, or interquartile range as appropriate. Categorical variables are described in absolute numbers and percentages. The statistical analysis of the quantitative variables, with independent groups, is performed with the parametric Student’s *t* test, providing that its conditions for application are met. Otherwise, the non-parametric Mann-Whitney *U* test is used. Statistical analysis for categorical variables is performed using the Pearson *χ*^2^ test or the Fisher exact test. Specifically, the above methods are used to compare the two groups in terms of baseline characteristics in order to assess whether the randomization has been effective. Ninety-five percent confidence intervals for the ratio will be reported. In all cases, the level of significance will be the usual 5% (*α* = 0.05).

This study has a low risk of selection bias due to the use of a computer random number generator. Central allocation and the use of sequentially numbered drug containers of identical appearance allow to achieve a low risk of deviations. Performance bias may be considered as having an average risk due to blinding only participants of the study, the personnel is not blinding. Blinding of outcome assessment is ensured, so detection bias is unlikely. Attrition bias could probably appear because of the difficulty of collecting data from patients outside the hospital or the refusal of future treatment and visiting the doctor during follow-up.

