### Interventions

#### Preoperative preparation

Two hours before the procedure, every patient receives a medication. The research group receives ketoprofen 100 mg per os; the control group receives a placebo.

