#### Postoperative period

After the procedure, all patients receive the standard analgesics scheme. It includes ketoprofen (the average dose, 100 mg per day; the maximum dose, 200 mg per day), paracetamol (at the maximum dose of 1000 mg per day), and local anesthetics with lidocaine before defecation. Patients are usually discharged on the 4–5th day after surgery when their pain level is below 5 points according to VAS. After discharge, a standard analgesics scheme mentioned above is recommended to all patients. If the pain level reaches 5–6 points according to VAS on the 5th day after the procedure, patients continue inpatient treatment and may receive an opioid analgesic.

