### The main outcome measures

The trial is conducted to evaluate the primary outcome: the quantity of the opioid administration intake per day during the first week postoperatively that is necessary to hold pain level no more than 3–4 VAS points in every patient. We use tramadol as an opioid analgesic in a single standard dose of 100 mg for patients with persistent severe pain syndrome in our clinic. The study also assesses the following secondary outcomes: (1) the pain severity before and after defecation according to VAS on the 6, 12, and 24 h after the procedure, then 2 times per day up to 7th postoperative day; (2) duration and (3) frequency of other analgesics intake (systemically and topically) during the first week postoperatively; (4) readmission rate and (5) overall quality of life on the 7th and 30th days; (6) time from the procedure to return to work; and (7) the complications rate (i.e. bleeding, retention of urine, infectious complications) in the early postoperative period (30 days after procedure). The pain severity, duration and frequency of other analgesics intake during the first week postoperatively will be assessed using “Postoperative protocol for pain management” (Additional file 2). The overall quality of life will be assessed with a patient-reported questionnaire Short Form 36 (SF-36). A total score in each of the 8 sections will be calculated and transformed into a 0–100 scale with a score of zero equivalents to maximum disability and a score of 100 equivalents to no disability. Other secondary outcomes will be updated during visits or by phone on the 7 and 30 days after the surgery.

All patients are scheduled to return to the ambulatory clinic on the 7 and 30 days after the surgery. During these visits, postoperative data is collected and digital rectal examination is performed. If a patient fails to follow up, the researcher may contact the patient by all means available (phone, email, or mail) to ascertain whether the patient has had any complications and/or adverse events that were treated at another hospital. If the researcher is unsuccessful in contacting the patient, the patient will be considered as lost to follow-up.

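### The per-protocol exclusions do not fit a one-tablet intervention and, as most naturally read, select patients on postoperative analgesic use, which is itself an outcome

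*Protocol article*

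**What the plan says.** - **Per-protocol set** (Statistics). The full analysis is reduced by removing "all the non-compliant patients, patients who received incomplete treatment, and patients who refused further treatment after randomization". The treatment meant is not named.
- **ITT set** (Statistics, preceding sentence). "The ITT analysis included all randomized patients treated for at least 1 week", with a further requirement of baseline and later efficacy evaluation.
- **Randomized intervention** (Preoperative preparation). "Two hours before the procedure, every patient receives a medication": ketoprofen 100 mg in one arm, placebo in the other, as a single oral dose.
- **Postoperative treatment, both arms** (Postoperative period). "After the procedure, all patients receive the standard analgesics scheme", made up of ketoprofen, paracetamol and lidocaine. After discharge, usually on day 4 or 5, "a standard analgesics scheme mentioned above is recommended to all patients".
- **Outcomes** (The main outcome measures). The primary outcome is "the quantity of the opioid administration intake per day during the first week postoperatively". The secondary outcomes include "2) duration and (3) frequency of other analgesics intake (systemically and topically) during the first week postoperatively".
- **Attrition** (Statistics, last paragraph). One expected source is "the refusal of future treatment and visiting the doctor during follow-up".

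**The concern.** A per-protocol set should keep patients who received the assigned strategy, judged by facts that the outcome cannot influence. Here the assigned strategy is finished before the operation starts. One tablet can be left untaken, but it is not a course that can be part-completed, and no later dose of it remains to be refused. Exclusions worded for a course of treatment therefore tend to attach to the only treatment that continues, the postoperative analgesics.

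The use of those analgesics is measured as an outcome. If a patient leaves the per-protocol set for stopping or declining them, the set is selected on secondary outcomes 2 and 3. It is also selected indirectly on pain and on opioid need, because patients with little pain and patients with poor tolerance are the ones likely to stop. If stopping differs by arm, the per-protocol comparison loses the balance that randomization gave it.

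**Working it through.** The plan states no figure on this point, so there is none to reproduce. The check has two parts.

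**1. What can treatment mean in the Statistics section?**

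| Term in Statistics | Applied to the tablet | Applied to the postoperative scheme |
|---|---|---|
| Treated for at least 1 week (ITT) | Impossible for a single dose | Fits |
| Incomplete treatment | Fits poorly: taken or not taken | Fits, but no required duration is stated |
| Refused further treatment after randomization | Fits only before the tablet or operation | Fits |
| Refusal of future treatment during follow-up | Does not fit: the tablet is already past | Fits, though it is tied to missed visits |
| Non-compliant | Fits: tablet not taken | Also fits |

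The one-week condition is the strongest clue, since only the postoperative course can last a week. The best-supported reading is that treatment includes that course. The Postoperative period section gives average and maximum doses for ketoprofen and a maximum for paracetamol, but no minimum duration. After discharge the scheme is only a recommendation, while the analgesic outcomes run through the first week. There is thus no benchmark for complete treatment, and early stopping is foreseeable.

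**2. What could selection on that course do to the opioid comparison?**

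Inputs from the Sample size section: control opioid use 20 to 30%, midpoint 25% used here; at most 10% with preemptive analgesia. The exclusion rates are assumptions; the documents give none.

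Let p be the true opioid rate, e1 the share of opioid users excluded and e0 the share of non-users excluded. The rate among those retained is

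p(1 − e1) / [p(1 − e1) + (1 − p)(1 − e0)].

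*No true effect, 25% in both arms, exclusions only among opioid-free patients (e1 = 0):*

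| e0 control / ketoprofen | Control | Ketoprofen | Ketoprofen minus control |
|---|---|---|---|
| 10% / 10% | 0.25/0.925 = 27.0% | 27.0% | 0 |
| 10% / 20% | 27.0% | 0.25/0.85 = 29.4% | +2.4 points |
| 5% / 30% | 0.25/0.9625 = 26.0% | 0.25/0.775 = 32.3% | +6.3 points |

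Swapping the exclusion rates between the arms reverses the sign.

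*True rates 25% v 10% (difference 15.0 points, relative risk 0.40), e1 = 0:*

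| e0 control / ketoprofen | Control | Ketoprofen | Difference | Relative risk |
|---|---|---|---|---|
| 5% / 20% | 26.0% | 0.10/0.82 = 12.2% | 13.8 points | 0.47 |
| 10% / 30% | 27.0% | 0.10/0.73 = 13.7% | 13.3 points | 0.51 |
| 10% / 10% | 27.0% | 0.10/0.91 = 11.0% | 16.0 points | 0.41 |

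*In patient counts.* Take 18/72 (25.0%) opioid users on placebo and 7/72 (9.7%) on ketoprofen. Suppose 15% and 30% of each whole arm are excluded, all opioid-free: 72 × 0.15 ≈ 11 and 72 × 0.30 ≈ 22. The rates become 18/61 = 29.5% and 7/50 = 14.0%. The relative risk moves from 0.39 to 0.47, while the risk difference hardly changes (15.3 to 15.5 points).

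The distortion can be zero, can narrow or widen the difference, and can look different on the two effect scales. The effect on outcomes 2 and 3 was not computed, because the documents give no distribution of analgesic duration.

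**The case against.** The strongest reply is that the wording is loose but need not reach the postoperative analgesics. Randomization follows consent, and the tablet, the spinal anesthesia and the operation all come later, so a patient can refuse any of these after randomization. Non-compliant has an obvious meaning, tablet not taken, and the protocol does not describe how intake is assured. The attrition sentence ties refusal to missed visits, which looks like withdrawal and not like taking fewer painkillers. With no stated duration for the scheme, a comfortable patient who stops on day 2 is not shown to be incompletely treated. If the scheme is what is meant, that patient already fails the one-week ITT condition. Finally, per-protocol sets always drop non-compliers, this one stands beside an ITT analysis in a superiority trial, and an article may leave itemized deviations to the full protocol or SAP.

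Much of this stands. A reader might infer that the rule definitely means stopping postoperative analgesics. The documents do not support that, because treatment is never defined. A reader might also infer that the selection must draw the arms together, or that the per-protocol result would carry no information. The figures above support neither: equal exclusions widened the difference, and the count example still shows a large benefit.

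Two things remain. The rule is stated in the article, so the complaint is not about omitted detail, and its terms suit a course of treatment better than a single tablet. The point about the day-2 stopper does not rescue the per-protocol set either; it shows that the set from which it is cut may carry the same selection.

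**Conclusion.** The point holds as a conditional one. The per-protocol rule does not say which treatment must be complete, and the wording around it most naturally brings in the postoperative analgesic scheme. On that reading, membership depends on analgesic use after randomization, which is directly secondary outcomes 2 and 3 and is related to pain and to the primary opioid outcome.

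The size cannot be fixed from the documents. Under the assumed exclusion rates, the spurious opioid difference with no true effect ranges from 0 to 6.3 points, and a true 15.0-point difference appears as 13.3 to 16.0 points. These figures rest on the 25% and 10% opioid rates taken from the Sample size section, on unsourced exclusion rates, and on only opioid-free patients being excluded.

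The consequence of this rule is limited to the per-protocol result. The one-week condition on the ITT set is a separate and more consequential flaw. It matters here because repairing the per-protocol sentence alone would leave the same selection in place.

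**What to change.** In the Statistics section:

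1. Define the per-protocol set only by facts fixed by the end of surgery: eligible, assigned tablet taken, spinal anesthesia achieved, Milligan-Morgan hemorrhoidectomy done.
2. Delete the exclusions for incomplete treatment and for refusal of later treatment. State that stopping or refusing postoperative analgesics is outcome data under secondary outcomes 2 and 3 and is no ground for exclusion.
3. Remove the one-week treatment condition from the ITT set.

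This prevents selection on analgesic use under either reading of the present text and changes no clinical rule.

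The cost is about two sentences, to be settled before the blinded analyst sees treatment codes. Patient history and operation notes already go into the eCRF. The article does not say whether tablet intake is recorded; if it is not, one eCRF field is needed.
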